### Registered Variables

2.10

The variables registered at baseline, daily during ICU admission, and at days 2, 4, and 90 are presented in Tables 3, 4, 5, respectively. Complete follow‐up during the 90‐day period for patients transferred to a non‐participating ICU or hospital will be obtained through mail or telephone contact.

**TABLE 3 aas70233-tbl-0003:** Baseline registrations.

Registration	Definition
Age	Calculated from birth date (years).
Sex	Legal sex, as defined by personal identification number in the Danish civil registration system (female/male).
Height	cm.
Weight	Absolute weight (kg).
Date of hospital admission	If transferred from a different hospital, the date of admission to the first hospital applies (ddmmyyyy).
Date and time of ICU admission	Date and time of admission to current ICU (ddmmyyyy, hh:mm).
Pre‐ICU location	(Emergency department or pre‐hospital setting/general ward/operating or recovery room/different ICU).
Surgery	Conducted during current hospitalisation (yes/no).
Surgery type^a^	Of last operation conducted (acute/elective).
Respiratory status	
Estimated pleural effusion size	Right and left side, measured between the parietal and visceral pleura perpendicularly to the chest wall at the largest separation point at randomisation (cm).
Type of respiratory support	At randomisation (Invasive ventilation/NIV including CPAP/oxygen on open systems).
Ventilator settings if invasively ventilated	FiO_2_ (fraction) at the time of the last ABG prior to randomisation, and peak pressure (cm H_2_O), tidal volume (ml) and positive end‐expiratory pressure (cm H_2_O) at the time of randomisation.
Ventilator settings non‐invasively ventilated (including CPAP)	FiO_2_ (fraction) at the time of the last ABG prior to randomisation, and end‐expiratory pressure (cm H_2_O) at randomisation.
If on open system	Type of system (nasal cannula/mask/non‐rebreather mask/T‐piece or speaking valve on tracheal cannula), flow (L/min) and fraction (decimal) of oxygen supplementation at the time of the last ABG prior to randomisation.
PaO_2_	Last ABG before randomisation (kPa).
SaO_2_	Last ABG before randomisation (%).
pH	Last ABG before randomisation.
PaCO_2_	Last ABG before randomisation (kPa).
p‐lactate	Highest plasma lactate measured in 24 h prior to randomisation (mmol/L).
Acute illness^b^	
Pneumonia^a^	As defined by clinicians and noted in the medical records (yes/no).
Side of pneumonia	As estimated by clinicians from radiographic imaging (right‐sided/left‐side/bilaterally).
Multiple trauma	Acute accident with lesions in two anatomical sites or more (yes/no).
Myocardial infarction	Verified by electrocardiographic changes, significant rise in coronary biomarkers, and/or acute PCI or CABG conducted (yes/no).
Cardiac arrest	Clinically diagnosed with initiated cardiopulmonary resuscitation, leading to or occurred during current ICU admission (yes/no).
ARDS	According to the Berlin definition [33] (yes/no).
Sepsis	According to the Sepsis 3 definition [34] (yes/no).
Site(s) of infection^a^	Suspected or confirmed (pulmonary/abdominal/urinary or genital/central nervous system/soft tissue/intravascular/unknown).
SMS‐ICU score [35]	
Systolic blood pressure	Lowest systolic arterial pressure in 24 h prior to randomisation (mm Hg).
Use of vasopressors or inotropes	In 24 h prior to randomisation, includes any continuous infusion of: norepinephrine, epinephrine, phenylephrine, vasopressin analogues, angiotensin, dopamine, dobutamine, levosimendan, or milrinone (yes/no).
Renal replacement therapy	Includes any renal replacement therapy whether chronic or acute, ongoing at the time of randomisation, days between intermittent haemodialysis are considered as with ongoing renal replacement therapy (yes/no).
Chronic co‐morbidity	
Ischaemic heart disease	Previous myocardial infarction, previously conducted PCI or CABG, or previous stable or unstable angina pectoris or use of nitrates indicating this (yes/no).
Chronic heart failure	Chronic LVEF ≤ 40% or diagnosed chronic heart failure with preserved LVEF (yes/no).
Active metastatic cancer	Any metastasis from a malignant non‐haematological neoplasm, which was not considered eradicated at randomisation (yes/no).
Active haematological malignancy	Defined from the World Health Organisation 2017 classification [36], is considered active if the diagnosis resulted in any interventions conducted within the last 6 months prior to randomisation (yes/no).
COPD	Defined as previous spirometry in stable phase diagnostic of COPD [37], or COPD in the anamnesis and daily use of inhaled β_2_‐adrenergic bronchodilators, anticholinergic bronchodilators or glucocorticoids (yes/no).
Chronic dialysis	Includes any renal replacement therapy initiated prior to current hospital admission of any kind, e.g., intermittent haemodialysis or peritoneal dialysis (yes/no).

Abbreviations: ABG: arterial blood gas analysis; ARDS: acute respiratory distress syndrome; CABG: coronary artery bypass grafting; COPD: chronic obstructive pulmonary disease; CPAP: continuous positive airway pressure; FiO_2_: fraction of inspired oxygen; ICU: intensive care unit; LVEF: left ventricular ejection fraction; NIV: non‐invasive ventilation; PaCO_2_: arterial partial pressure of carbon dioxide; PaO_2_: arterial partial pressure of oxygen; PCI: percutaneous coronary intervention; SaO_2_: arterial oxygen saturation of haemoglobin; SMS‐ICU: Simplified Mortality Score for the Intensive Care Unit.

^a^
Only registered if ‘yes’ to previous registration.

^b^
Must have led to or occurred during current hospitalisation.

**TABLE 4 aas70233-tbl-0004:** Daily registrations during ICU admission.

Registration	Definition
Pleural drainage on this day	Includes all types of pleural drainage, e.g., pig‐tail catheter insertion, surgical drainage, or diagnostic pleural tap (yes/no).
Procedure details^a^	Side of pleural drainage (left/right/bilateral), time of drainage (hh:mm), drainage conducted by (radiologist/intensivist/surgeon/other), indication for drainage (pleural effusion ≥ 2 cm in intervention group/haemothorax/pneumothorax/pleural infection/pleural malignancy/invasive or non‐invasive ventilation and PaO_2_:FiO_2_ ratio ≤ 13.3 kPa/high‐flow oxygen therapy with flow ≥ 50 L/min and PaO_2_:FiO_2_ ratio ≤ 13.3 kPa/respiratory acidosis despite non‐invasive ventilation for > 1 h/other).
Pleural catheter or drain in situ on this day	Includes catheters or drains inserted or removed on this day (yes/no).
Drainage details^a^	Side of drain (left/right/bilateral), 24‐h fluid output (mL), pleural catheter removed (yes/no) with time (hh:mm) of removal.
PaO_2_	In the ABG conducted closest to 20:00 in ICU (kPa).
SaO_2_	In the ABG conducted closest to 20:00 in ICU (%).
Type of oxygen supplementation	At the time of the ABG conducted closest to 20:00 in ICU (closed system/open system/none).
FiO_2_ if closed system	At the time of the ABG conducted closest to 20:00 in ICU (fraction).
Oxygen supplementation if open system	Type of system (nasal cannula/mask/non‐rebreather mask/T‐piece or speaking valve on tracheal cannula), flow (L/min) and fraction (decimal) of oxygen supplementation, at the time of the ABG conducted closest to 20:00 in ICU.
PaCO_2_	Highest PaCO_2_ measured on this day in ICU (kPa).
pH	In the ABG with the highest PaCO_2_ on this day in ICU.
Mechanical ventilation	Any use of NIV, continuous mask CPAP, or invasive mechanical ventilation (yes/no). Intermittent CPAP does not count as mechanical ventilation.
PEEP, EPAP or CPAP^b^	Setting closest to 20:00 (cm H_2_O).
Tidal volume^c^	Measurement closest to 20:00 (ml).
Peak pressure^c^	Measurement closest to 20:00 (cm H_2_O).
Mechanical ventilation in prone position	Any proning of the patient due to respiratory failure (yes/no).
Continuous infusion of vasopressors or inotropes	Includes norepinephrine, epinephrine, phenylephrine, vasopressin analogues, angiotensin, dopamine, dobutamine, levosimendan, or milrinone (yes/no).
Renal replacement therapy	Any continuous or intermittent renal replacement therapy (yes/no). Days between any intermittently used renal replacement therapy counts as ‘yes’.
Use of any diuretics	(yes/no).
Diuretic type and dose^a^	Cummulated dose of furosemide (mg), thiazides (mg), spironolactone (mg) other—describe (mg).
Serious adverse events	
Pneumothorax	Any pneumothorax on this day requiring invasive treatment with drainage or surgery (yes/no).
Haemothorax	Any haemothorax on this day, or other haemorrhagic complication to pleural drainage, requiring red blood cell transfusion (yes/no).
New episode of invasive mechanical ventilation	Endotracheal intubation or re‐intubation after extubation or tracheal decannulation on this day (yes/no). Tracheotomy on already intubated patient, endotracheal tube exchange does not count as a new episode of invasive mechanical ventilation. Intubation in relation to surgical procedures does not count as a new episode of invasive mechanical ventilation, unless the patient is transferred to the ICU whilst still intubated after surgery.

*Note:* Daily variables are registered from 06:00 to 06:00 whilst admitted to the ICU for up to 90 days, starting at the time of randomisation and including readmissions.

Abbreviations: ABG: arterial blood gas analysis; CPAP: continuous positive airway pressure; EPAP: expiratory positive airway pressure; FiO_2_: fraction of inspired oxygen; ICU: intensive care unit; NIV: non‐invasive ventilation; PaCO_2_: arterial partial pressure of carbon dioxide; PaO_2_: arterial partial pressure of oxygen; PEEP: positive end‐expiratory pressure; SaO_2_: arterial oxygen saturation of haemoglobin.

^a^
Only registered if ‘yes’ to previous registration.

^b^
Only registered if mechanically ventilated on this day.

^c^
Only registered if ‘invasive’ mechanical ventilation closest to 20:00.

**TABLE 5 aas70233-tbl-0005:** Registrations on day 2 and 4, and at 90‐day follow‐up.

On day 2 and 4	
Registration	Definition
PaO_2_	In the ABG conducted in ICU closest to 24 h and 72 h after randomisation, respectively (kPa).
SaO_2_	In the ABG conducted in ICU closest to 24 h and 72 h after randomisation, respectively (kPa).
Type of oxygen supplementation	At the time of the ABG conducted in ICU closest to 24 h and 72 h after randomisation, respectively (closed system/open system/none).
FiO_2_ if closed system	At the time of the ABG conducted in ICU closest to 24 h and 72 h after randomisation, respectively (fraction).
Oxygen supplementation if open system	Type of system (nasal cannula/mask/non‐rebreather mask/T‐piece or speaking valve on tracheal cannula), flow (L/min) and fraction (decimal) of oxygen supplementation, at the time of the ABG conducted in ICU closest to 24 h and 72 h after randomisation, respectively.
PaCO_2_	In the ABG conducted in ICU closest to 24 h and 72 h after randomisation, respectively (kPa).
pH	In the ABG conducted in ICU closest to 24 h and 72 h after randomisation, respectively (kPa).

At 90‐day follow‐up	
Registration	Definition
Pneumothorax outside the ICU	Any pneumothorax requiring invasive treatment with drainage or surgery within 90 days from randomisation (yes/no).
Haemothorax outside the ICU	Any haemothorax, or other haemorrhagic complication to pleural drainage, requiring red blood cell transfusion within 90 days from randomisation (yes/no).
Blood stream infection	Any blood culture conducted within 90 days from randomisation, with growth of any microorganism except microorganisms clearly specified to be contaminants or likely contaminants by the microbiological department (yes/no). If yes, species and genus of microorganism(s) cultured (descriptive).
Pleural infection	Any pleural fluid culture of any fungi or bacteria, except coagulase negative Staphylococci, Enterococci, and *Corynebacterium* species, in any pleural fluid sampling conducted after 24 h after within 90 days from randomisation (yes/no). If yes, species and genus of microorganism(s) cultured (descriptive).
Pleural drainage outside the ICU	Within 90 days from randomisation, includes all types of pleural drainage, e.g., pig‐tail catheter insertion, surgical drainage, or diagnostic pleural tap (yes/no).
New invasive mechanical ventilation in non‐participating ICU	Endotracheal intubation, or re‐intubation after extubation or tracheal decannulation within 90 days from randomisation conducted in or with transfer to non‐participating ICU (yes/no). Tracheotomy on already intubated patient and endotracheal tube exchange does not count as a new episode of invasive mechanical ventilation. Intubation in relation to surgical procedures does not count as a new episode of invasive mechanical ventilation, unless the patient is transferred to the ICU whilst still intubated after surgery.
Days with mechanical ventilation outside participating ICU	Days from 06:00 to 06:00 with any use of NIV, continuous mask CPAP, or invasive mechanical ventilation in non‐participating ICU, on general ward, or after discharge from hospital in 90 days from randomisation (number of days). Intermittent CPAP does not count as mechanical ventilation. Nocturnal CPAP due to sleep apnoea or obesity‐hypoventilation syndrome does not count as mechanical ventilation.
Days with vasopressors outside participating ICU	Days from 06:00 to 06:00 with any use of norepinephrine, epinephrine, phenylephrine, vasopressin analogues, angiotensin, dopamine, dobutamine, levosimendan, or milrinone in non‐participating ICU in 90 days from randomisation (number of days).
Days with renal replacement therapy outside participating ICU	Days from 06:00 to 06:00 with any continuous or intermittent renal replacement therapy in non‐participating ICU, at general ward or after discharge from hospital in 90 days from randomisation (number of days). Days between any intermittently used renal replacement therapy counts as with renal replacement therapy.
Discharge from hospital	Within 90 days from randomisation (yes/no).
Date of hospital discharge^a^	(ddmmyyyy).
Readmission to hospital^a^	Within 90 days from randomisation (yes/no).
Dates of readmissions^b^	Number of readmissions (*n*) and dates of readmission and discharge for each hospital readmission within 90 days from randomisation (ddmmyyyy).
Dead	Death by any cause within 90 days from randomisation (yes/no).
Date of death^c^	(ddmmyyyy).

Abbreviations: ABG: arterial blood gas analysis; FiO_2_: fraction of inspired oxygen; ICU: intensive care unit; PaCO_2_: arterial partial pressure of carbon dioxide; PaO_2_: arterial partial pressure of oxygen; SaO_2_: arterial oxygen saturation of haemoglobin.

^a^
Only registered in ‘yes’ to ‘discharge from hospital’.

^b^
Only registered if ‘yes’ to ‘readmission to hospital’.

^c^
Only registered if ‘yes’ to ‘dead’.

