### Withdrawal and Discontinuation of Trial Intervention

2.8

If informed consent is not given or retracted at any time (according to Danish regulations), the patient will be withdrawn from the trial. Data registration for a withdrawn patient will continue if consent for this is given. Only the trial participant can demand deletion of already registered data. If so, all data will be deleted, and a new participant will be enrolled to obtain the full sample size.

Clinicians or investigators may deviate from the allocated pleural drainage strategy if the participant experiences intolerable adverse events suspected to be related to the allocated trial intervention or the clinicians in conjunction with the coordinating centre decide it to be in the best interest of the patient. In such cases the patient remains in the trial and the allocated strategy of pleural drainage will be reinstated as soon as it is considered acceptable within 90 days. If a patient after inclusion is subject to involuntary hospitalisation and treatment, the continued strategy of pleural drainage will follow local standards. The collection of data and follow‐up will continue, and the participant will remain in the intention‐to‐treat population.

Participants who are discharged to another ICU will be regarded as discharged from the ICU unless the receiving ICU is an active DOPE‐ICU feasibility trial site. If so, the patient will keep the allocated pleural drainage strategy during ICU admission up until 90 days after randomisation. All patients will be followed up for all outcomes.

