#### Secondary Clinical Outcomes

2.9.2

All‐cause mortality within 90 days from randomisation.Proportions of patients with one or more serious adverse events within 90 days from randomisation defined as: (1) new pneumothorax requiring invasive treatment (drainage or surgery), (2) new haemothorax requiring red blood cell transfusion or other haemorrhagic complication related to pleural drainage requiring red blood cell transfusion, (3) new blood stream infection defined as any cultured microorganism from any blood sample except microorganisms clearly specified to be contaminants or likely contaminants by the microbiological department, and (4) new episode of invasive mechanical ventilation defined as endotracheal intubation or re‐intubation after extubation or tracheal decannulation.Absolute number of days alive without life support being the use of mechanical ventilation, renal replacement therapy, or circulatory support in the 90‐day period. Mechanical ventilation is defined as invasive or non‐invasive mechanical ventilation or CPAP. Intermittent CPAP is not considered mechanical ventilation. Renal replacement therapy is defined as any form of renal replacement therapy. In patients receiving intermittent renal replacement therapy, days between treatments are included as being with the use of renal replacement therapy. Circulatory support is defined as the use of continuously infused dopamine, norepinephrine, epinephrine, phenylephrine, vasopressin analogues, dobutamine, milrinone or levosimendan.Absolute number of days alive and out of hospital in the 90‐day period.

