#### Outcome Analyses

2.14.3

The primary outcome will be analysed using a generalised linear model with a log‐link and Poisson data distribution according to the relation between variance and mean, and a robust variance estimation adjusted for the stratification variable trial site. Significance of the intervention will be assessed based on the *p*‐value from this regression and reported with the readily available risk ratio with 95% confidence interval. A *p*‐value below 0.05 will be considered statistically significant. A similar analysis, however, with an identity‐link and Poisson data distribution instead to produce the risk difference with 95% CI, will be conducted as well. Dichotomous secondary outcomes will be analysed similarly to the primary outcome; however, no *p*‐values will be reported given the lack of power and explorative nature of these outcomes. Continuous and ordinal secondary outcomes will be analysed using a generalised linear model with an identity‐link, Gaussian data distribution and a robust variance estimation, adjusted for the stratification variable trial site to produce a mean difference with 95% CI. A generalised linear model will be applied, regardless of expected non‐normal data distribution of the residuals. Similarly to the other secondary outcomes, no *p*‐values will be reported.

Additional per‐protocol sensitivity analyses will be conducted for all secondary clinical and process outcomes, excluding patients with one or more protocol violations as defined under secondary feasibility outcome (a).

For the secondary clinical outcome (e) proportion of patients with one or more serious adverse events, a supplemental analysis will be conducted in which death from any cause within 90 days will be included as a serious adverse event.

For the secondary clinical outcome (f) number of days alive without life support, a supplemental analysis will be conducted in which patients who die within 90 days will be assigned a value of 0 days alive without life support.

For the secondary process outcomes (i), (j), and (k), supplemental analyses will be conducted investigating differences in the PaO_2_:FiO_2_ ratio, PaCO_2_ and pH, respectively, between individual baseline and 72‐h measurements.

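### Three undated support-day totals outside participating ICUs do not fix days alive without life support for patients with two or more non-zero totals

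*Protocol article*

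**What the plan says.** Section 2.9.2 of the protocol article defines outcome (f) as "Absolute number of days alive without life support being the use of mechanical ventilation, renal replacement therapy, or circulatory support", counted over 90 days. Section 2.14.3 analyses it with a Gaussian identity-link model "adjusted for the stratification variable trial site to produce a mean difference with 95% CI", so each patient must contribute one value.

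The data come from two forms. In participating ICUs, Table 4 records each support as yes or no per day: "Daily variables are registered from 06:00 to 06:00 whilst admitted to the ICU for up to 90 days", including readmissions. Outside them, Table 5 has three separate items at the 90-day follow-up:

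- ventilation days in a non-participating ICU, "on general ward, or after discharge from hospital in 90 days from randomisation (number of days");
- "Days with vasopressors outside participating ICU", limited to non-participating ICUs;
- "Days with renal replacement therapy outside participating ICU", which also covers days "at general ward or after discharge from hospital in 90 days from randomisation (number of days") and counts the days between intermittent sessions.

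The only dates on the 90-day form are for hospital discharge, readmission and death. Section 2.8 treats transfer to a non-participating ICU as ICU discharge but adds "All patients will be followed up for all outcomes".

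**The concern.** A day on two or three supports is one lost day, not two or three. The outcome therefore needs the union of the support days, and three undated totals do not determine a union. Adding them counts shared days more than once; taking the largest misses days when the supports were used at different times. Two analysts could derive different values for the same patient from the same record. A later analysis plan cannot recover overlap that was never recorded.

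At stake is the accuracy of one exploratory clinical outcome, and a form that could be carried into the definitive trial this study is meant to inform.

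**Working it through.** **Inputs.** The outcome definition is in section 2.9.2, the field formats are in Tables 4 and 5, and the arm size is 88/2 = 44 from the planned total and 1:1 allocation. The article states no figure for outcome (f), so there is none to reproduce. The day totals below are illustrative assumptions.

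**Bounds.** Let m, v and r be the ventilation, vasopressor/inotrope and renal-replacement totals outside participating ICUs, and T the days alive outside them within the 90 days. The number of any-support days U satisfies

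max(m, v, r) ≤ U ≤ min(T, m + v + r).

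U is exact only when the two ends meet. That happens if only one total is non-zero, so that the sum equals the maximum, or if one support covers every day, so that the maximum equals T.

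| m / v / r | T | U | Support-free days (T − U) |
|---|---|---|---|
| 10 / 8 / 5 | 23 or more | 10 to 23 | range of 13 days |
| 8 / 5 / 6 | 20 | 8 to 19 | 1 to 12 |
| 8 / 5 / 0 | 20 | 8 to 13 | 7 to 12 |
| 8 / 0 / 0 | 20 | 8 | 12, exact |
| 10 / 5 / 30 | 30 | 30 | 0, exact |

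The cap matters. With totals of 10/8/5 but T = 15, U runs from 10 to 15, a width of 5 days instead of 13.

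**Effect on an arm mean.** One patient with the full 13-day width shifts the mean of 44 patients by at most 13/44 = 0.295, about 0.3 days.

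**Effect on the reported contrast.** If one rule is used in both arms, and a and b patients in the two arms each have that width, switching between the extreme rules changes the unadjusted difference in means by 13(a − b)/44. With equal numbers the shift cancels.

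**Scale.** The article gives no standard deviation for outcome (f). Assuming 20 to 35 days, the standard error of the difference is SD × √(2/44), about 4.3 to 7.5 days. A shift of 0.3 days is then about 0.04 to 0.07 standard errors.

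**The case against.** **Few patients are likely to be exposed.** All days in participating ICUs are recorded day by day, including readmissions. Vasopressor days outside are collected only for non-participating ICUs, so three non-zero totals can arise only in patients treated in one. No transfer rate is given. This stands and limits the size of the problem.

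**The outcome is exploratory and analysed masked.** No p-values are reported for secondary outcomes, and section 2.11 has them analysed with groups coded and before the primary outcome is extracted. A combining rule is therefore unlikely to be picked to favour an arm. This also stands, but masking does not supply the missing overlap. The supplemental analysis that assigns 0 days to patients who die removes the ambiguity for them in that analysis only.

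**The article is a condensed source.** The full protocol or form may hold a rule for combining the totals, and its absence here is not held against the plan. The point rests on the field format, which Table 5 does state.

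**Stronger readings that the documents do not support.** A reader might infer that the outcome cannot be calculated for anyone with overlapping supports. That goes too far: the value is exact when one support covers every day outside, as in continuing dialysis. Conversely, patients whose supports did not overlap are affected too, because the form cannot tell the two situations apart. A reader might also assume that 5–10% of patients are affected and multiply by 13 to get 0.65 to 1.3 days. That combines a rate the article does not give with the full width for every patient, and it describes one arm's mean, not the between-arm difference. Nor does the article say that the affected patients are the sickest.

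**Conclusion.** The point holds as a limited data-capture flaw. For patients with two or more non-zero totals outside participating ICUs, outcome (f) is in general known only within bounds, and the planned fields cannot narrow them. An illustrative patient with totals of 10/8/5, and at least 23 days alive outside, has a 13-day range and moves an arm mean by at most about 0.3 days. The total effect depends on how many such patients there are and how they divide between arms, neither of which the article gives; the number is probably small. The primary outcome, the sample size and the day-level data from participating ICUs are unaffected. The change is still worth making because it is cheap and because the form may be reused in the definitive trial.

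**What to change.** Add one item to the 90-day follow-up form: the number of days, 06:00 to 06:00, with any of mechanical ventilation, vasopressor/inotrope or renal replacement therapy outside participating ICUs. Start and stop dates for each support would serve equally well. Derive outcome (f) from this, and query only participants with two or more non-zero totals. Where the overlap cannot be recovered, fix one combining rule before unmasking and report outcome (f) at both bounds as a sensitivity analysis.

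The cost is one eCRF field and a few retrospective queries. Some will need new contact with outside units, because many participants are probably past day 90. The first patient was included on 3 December 2024 and 76 had been randomised by 11 March 2026, 463 days later. At an assumed uniform rate, 76 × (463 − 90)/463 ≈ 61 had completed 90 days by then. The combining rule and the analysis at the bounds need no new data.
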